**Figure 7 figure7:**
[figure not shown]
The consolidated standards of reporting trial flowchart. PIBQ: Parent-Infant Bonding Questionnaire; PES: Parenting Efficacy Scale; EPDS: Edinburg Postnatal Depression Scale; STAI: State-Trait Anxiety Inventory; PSSP: Perceived Social Support for Parenting; and WBPL: What Being the Parent of a Baby is Like.

Qualitative data will be analyzed using thematic analysis [57,58]. All recorded audio will be transcribed verbatim by the RA2 concurrently with data collection to capture nonverbal information. Transcribed data will be classified into different categories, with similar ideas grouped in a category highlighted in the same color. Related codes or categories will be collated together to form subthemes, which will be reviewed and combined to form themes [57]. Two investigators will be involved in the analysis process to compare and discuss the categories, subthemes, and themes that are generated and to achieve consensus. Rigor or trustworthiness, including credibility, transferability, dependability, and confirmability, will be considered carefully [58].

### Ethical Considerations

Ethics approval has been obtained from the National Health Group Domain Specific Review Board (NHG DSRB) before the commencement of the study (Ref. No: NHG DSRB: 2016/00651) in June 2016. All participants are given a set of participant information sheets consisting a brief introduction and the purpose of the study, with the advantages and disadvantages of the study conveyed clearly. The participants are guaranteed anonymity and are informed of the right to withdraw at any point of the study without affecting any subsequent care received.

## Results

Phase 1 of the study has been completed. Educational materials for both antenatal and postnatal education, audio and videos files, and the mHealth app have been developed. For phase 2, the recruitment of study participants commenced in December 2016 and is still ongoing. The targeted aim of recruiting 118 couples will be ongoing for a period of 12 months. The total number of participants approached thus far are 211, and 162 were screened (not interested and did not comply to one of the inclusion criteria). The current enrollment is 49 couples (for both the intervention [n=27] and control [n=22] groups). The projected timelines for the completion of the data entry and analysis for investigating the SEPP’s effectiveness on parental outcomes is around December 2017.

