**Methods:**

A randomized controlled two-group pretest and repeated posttest experimental design will be used. The study will recruit 118 parents (59 couples) from the antenatal clinics of a tertiary public hospital in Singapore. Eligible parents will be randomly allocated to receive either the supportive educational parenting program or routine perinatal care from the hospital. Outcome measures include parenting self-efficacy, parental bonding, postnatal depression, social support, parenting satisfaction, and cost evaluation. Data will be collected at the antenatal period, immediate postnatal period, and at 1 month and 3 months post childbirth.

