## Methods

### Design

A randomized controlled two-group pretest and repeated posttest experimental design will be used. Couples (n=118 participants) recruited from a tertiary hospital will be randomly assigned into the two groups (intervention group receiving the SEPP and routine care or control group receiving only routine care). Data will be collected via questionnaire surveys using locally validated and reliable instruments, medical reviews, semistructured face-to-face interviews, and telephone interviews.

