### Participants

The participants recruited will be couples (a father and mother dyad is considered one couple). The inclusion and exclusion criteria for participants who are mothers are shown in Textboxes 1 and 2.

The inclusion criteria for fathers are those who (1) are 21 years and above, (2) are able to read and speak English, (3) have a mobile phone with Internet access, and (4) plan to stay in Singapore for the first 3 months post delivery. The exclusion criteria for fathers are those who have self-reported physical or mental disorders that will interfere with their ability to participate in the study and/or are a single parent.

All couples are recruited antenatally and will be told beforehand that they may be excluded from the study if mothers are to experience complication during their pregnancy and the delivery of their newborn.

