### Sample Size Determination

On the basis of previous studies, psychosocial and educational interventions in the perinatal period generally produce a medium size effect on outcome variables [27,28]. Hence, the SEPP intervention can also be assumed to have a medium effect size on outcome variables. A repeated measure analysis of covariance (ANCOVA) will be used to test for differences between two groups (intervention and control) and within four separate time points and for interaction (group x time) effects. The required sample size for the detection of a medium effect size of 0.3 (analysis of variance [ANOVA] *F* value) at a power of 80% and a significance level of 5% (two-sided) is 45 in each group [40]. Considering a 30.0% (30/100) attrition rate based on previous studies [27,29], a minimum of 118 participants (45x2 + 45x2x30%=90 + 28=118), with 59 in each group, is needed. A purposive sample of approximately 16 participants will be needed for the process evaluation. Parents with differing mean parenting efficacy (primary outcome) scores from both the intervention and control groups (8 from each group) will be selected to participate in the face-to-face interviews, until data saturation is attained.

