### Randomization

The research randomizer will be used to randomly generate one set of 59 numbers ranging from 1 to 118. Generated numbers are assigned to the intervention group and the remaining to the control group. All 118 numbers will be placed in an opaque envelope. The principle investigator who will not be involved in the recruitment will hold the random numbers and pass it to RA1 for recruitment. After assessing eligibility and obtaining informed consent, the participants will be asked to pick a number from the opaque envelope, in which the number picked will determine the groups assigned.

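### The recruitment target is given both as 118 parents (59 couples) and as 118 couples, and the unit that is randomised is worded inconsistently

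*Protocol article*

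**What the plan says.** On the target:

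- Abstract, Methods: "The study will recruit 118 parents (59 couples) from the antenatal clinics of a tertiary public hospital in Singapore".
- Design: "Couples (n=118 participants) recruited from a tertiary hospital will be randomly assigned into the two groups". No number of couples is given.
- Sample Size Determination: 45 per group for an effect size of 0.3 at 80% power, raised for 30% attrition to a minimum of 118 participants, "with 59 in each group, is needed". No number of couples is given here either.
- Results: "The targeted aim of recruiting 118 couples will be ongoing for a period of 12 months". The same paragraph reports 49 couples enrolled, 27 in the intervention group and 22 in the control group.

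On the unit that is randomised:

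- Abstract, Methods: "Eligible parents will be randomly allocated to receive either the supportive educational parenting program or routine perinatal care from the hospital".
- Design: couples are assigned (quoted above).
- Participants: the people recruited are described as couples, but the same section goes on to speak of participants who are mothers and sets separate criteria for fathers.
- Randomization: 59 of the numbers 1 to 118 are assigned to intervention and the rest to control. After consent, "the participants will be asked to pick a number from the opaque envelope, in which the number picked will determine the groups assigned". Whether a couple draws once or each parent draws is not said.

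**The concern.** One hundred and eighteen parents and 118 couples cannot both be the target. The full protocol behind the article could show which is meant, but it could not make both statements true, so this is a contradiction and not an effect of condensing.

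The target fixes when recruitment stops and what power the trial has. From 49 enrolled couples, the trial needs 59 − 49 = 10 more on one reading and 118 − 49 = 69 more on the other.

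The unit matters because the programme is meant for both parents. If parents drew separately, a control parent could share a home with a partner who has the app and the education sessions. That contamination would pull the comparison towards no effect. The unit also decides whether 59 per group counts parents or couples.

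**Working it through.** **Reproducing the plan's figure.** Inputs from Sample Size Determination: f = 0.3 (for two groups d = 2f = 0.6), two-sided 5%, power 80%.

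- Between-group F test with two groups: 45 per group gives 80.4% power. The stated 45 reproduces.
- Attrition: 45 × 1.3 = 58.5, rounded up to 59 per group, 118 in total. (The text writes 28 for 90 × 30%, which is 27. The total is unaffected if each group is rounded up.)

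The formula treats the 45 per group as independent individuals.

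**Distance to target.** 49/59 = 83%; 49/118 = 42%.

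**Fitting each reading to the text.**

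1. *118 parents, each drawing a number.* The 118 numbers and 59 per group fit. Couples can then be split: 2 × (59/118) × (59/117) = 59/117 = 0.504 per couple, or 59 × 0.504 ≈ 30 of 59 couples expected. The reported counts of whole couples by arm do not fit.
2. *59 couples, one draw each.* The Abstract's target fits. Only half the numbers would be used, and 59 parents per arm would be 59/2 = 29.5 couples, which whole couples cannot give.
3. *118 couples, one draw each.* The number list, 59 per group (as couples) and the Results target fit. The Abstract's 118 parents (59 couples) is then wrong, and the 118 in Sample Size Determination counts couples, not parents.

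No reading fits every section.

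**Power under the two targets.** Assumptions: d = 0.6, 30% attrition, couples intact with both parents analysed, a single between-group comparison, normal approximation, and variance inflated by 1 + ICC for clusters of two. The documents give no within-couple ICC, so 0 to 0.5 is an assumed range.

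Power = Φ(0.6 × √(m/2) − 1.96), where m is retained parents per arm divided by (1 + ICC). Retained parents per arm are 59 × 0.7 = 41.3 with 59 couples and 118 × 0.7 = 82.6 with 118 couples.

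| ICC | 59 couples | 118 couples |
|---|---|---|
| 0 | 77.8% | 97.1% |
| 0.2 | 70.2% | 94.1% |
| 0.5 | 60.5% | 88.3% |

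With one parent per couple analysed, retained numbers per arm are 20.65 and 41.3, and power is 48.7% and 77.8%.

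The 77.8% at ICC 0 is below 80% because multiplying by 1.3 does not offset a 30% loss: 59 × 0.7 = 41.3, not 45. That shortfall is separate from the question of couples.

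**The case against.** The best defence is that the unit is named and one coherent plan can be recovered. Design says couples are assigned, and Participants says "The participants recruited will be couples (a father and mother dyad is considered one couple"). If participants means couples throughout, then 118 numbers, 59 per arm, one draw per couple and a target of 118 couples agree, and only the Abstract is out of line. The screening figures support this use of the word: 211 participants approached less 162 leaves 49, which is the number of couples.

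Much of this stands. It rules out calling the unit undefined, and it means that counting enrolment in couples does not show the trial departing from its written plan. It does not settle the target. The Abstract's 118 parents (59 couples) is explicit, the Abstract says parents are allocated, and the Participants section itself also uses the word for individuals.

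A reader might infer from the wording of the draw that couples are being split, with about half divided between arms. The documents do not support that. Couples are recruited and consented together, and the arm counts 27 + 22 = 49 leave no split couples. The 50% figure describes a literal draw by each parent and is not an estimate of what has happened.

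A reader might also make much of unequal arms if 59 couples drew from 118 numbers. That applies only under the 59-couple target, and its cost is small. Even a split of 24 and 35 couples keeps 4 × 24 × 35/59² = 96.5% of the efficiency of equal arms.

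**Conclusion.** The target is wrong as written. Current text gives two incompatible figures, 59 couples in the Abstract and 118 couples in Results, and this must be corrected because recruitment is under way. The twofold difference rests on the text alone. The loss of power from taking the smaller target, roughly 19 to 28 percentage points with both parents analysed, rests on the assumed ICC range and on the simplified single-comparison model; the repeated-measures analysis would change the levels.

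The randomised unit is inconsistently worded, not undefined. Splitting of couples is permitted by a literal reading of the Abstract and Randomization, but nothing shows that it occurs. Nor do all the sections with 118 side with 59 couples: only the Abstract gives that number, and Design and Sample Size Determination say participants.

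**What to change.** State one target, in couples and in parents, identically in the Abstract, Design, Sample Size Determination, Randomization and Results. In Randomization, state that each couple makes one draw and both parents go to the same arm. Then:

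- **If the target is 118 couples (236 parents):** correct the Abstract and the participant counts in Design and Sample Size Determination, and keep the existing list of 118 numbers, which already fits.
- **If the target is 59 couples (118 parents):** correct Results, use a number list sized to the couples for those not yet randomised, drop 59 in each group as a count of parents, and restate the power for that size, allowing for correlation within couples.

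The cost is wording and, under the second option only, a new list for the remaining couples (10 at the enrolment reported). Neither option needs more families than a target that the article already states.

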## Discussion

Theoretical framework–based and technology-enhanced educational programs have shown effectiveness [22,24,25,30,31] in influencing parental outcomes in the postnatal period. Previous studies have used varied technologies including telephone calls [31], Web-based programs [30], and mHealth apps [22,25] to influence postnatal depression [31], parenting satisfaction, and self-efficacy [30]. The only local study [25] that has used an mHealth app in supporting parents has influenced parental outcomes. However, the effectiveness was tested short-term (1 month post childbirth), and the study showed no influence on parental postnatal depression. A few studies [22,24,25,30,31] recommended the need of providing long-term perinatal educational support to parents. Specifically, the previous local study [25] recommended a long-term evaluation of the effectiveness of the educational program beyond 1 month. As such, this study will address this gap in literature by providing empirical support for the feasibility and effectiveness of the SEPP in enhancing parental outcomes across the perinatal period. This will also be the first study in Singapore that will examine the cost-effectiveness of an educational intervention delivered to parents.

We are hopeful that the provision of this technology-based educational program, which includes telephone calls and an mHealth app, will provide a clinically useful and potentially cost-effective solution to improve parental outcomes. This may eventually lead to more positive perinatal parenting experiences, which may influence the psychosocial well-being of both parents and their newborn, leading to better family dynamics and reducing associated health care and social burdens. It may also impact the future reproductive decisions of parents.

It is worthy to note that this study is being tested in a multiracial population, which enhances its relevance in the local context as participants in the study venue have similar demographic profile to Singapore’s general population, with the majority of its population being Chinese, followed by Malays and Indians. However, being a single-centered study, it limits its generalizability to an international population and requires further evaluation.

## Abbreviations

ANCOVA: analysis of covariance
EPDS: Edinburg Postnatal Depression Scale
HCP: health care professional
ITT: intention to treat
mHealth: mobile health
PES: Parenting Efficacy Scale
PIBQ: Parent-Infant Bonding Questionnaire
PSE: parenting self-efficacy
PSSP: perceived social support for parenting
RA: research assistant
SEPP: Supportive Educational Parenting Program
STAI: State Trait Anxiety Inventory
WBPL: What Being the Parent of a Baby is Like
